### Pre-specified subgroup analysis

Pre-specified subgroup analyses will use the statistical test for interaction and where appropriate, results will be presented as differences in means with 95% CIs, and the number needed to treat to benefit or harm calculated. Pre-specified subgroups will be based on:
Serum BA at baseline (< 100 μmol/L, ≥100 μmol/L).Site

### Dealing with missing data

Missing data as a result of women or babies being lost to follow-up are expected to be minimal. A sensitivity analysis will be conducted on the primary outcome and multiple imputation by the fully conditional specification (chained equations) method will be used to impute missing outcome data.

## Ethics & Regulatory Approvals

### Declaration of Helsinki and guidelines for good clinical practice

The trial is being conducted in compliance with the principles of the Declaration of Helsinki (1996), the ICH guidelines of Good Clinical Practice (GCP) and in accordance with all applicable regulatory requirements.

### Approvals

The trial has started after gaining approval from the registered HREC of the Women’s and Children’s Health Network and other relevant regulatory authorities, including the Therapeutic Goods Administration (TGA) (Australia), the Medicines and Healthcare products Regulatory Authority (MHRA) (UK) and the European Medicines Agency (EMA). Additionally, approval of local health service Research Offices is being sought for individual trial sites.

### Participant confidentiality, data handling and record keeping

Overall responsibility for ensuring that each participant’s information is kept confidential lies with the Site Investigator. All paper documents are being stored securely and kept in strict confidence in compliance with the Data Protection Act (1998) and all trial data are being stored in line with the UK Medicines for Human Use (Clinical Trials) Amended Regulations 2006) as defined in the KHP-CTO Archiving Standard Operating Procedure (SOP).

Data entered onto the eCRFs are being downloaded for storage and analysis into an electronic database held by The University of Adelaide in which the participant is identified only by a trial specific number and their initials. The participant’s name and any other identifying details are being stored in a separate database maintained by the site which will be linked only to the database containing study data by the participant’s trial number.

Electronic files are being stored on a file server that has restricted access. Data are being processed on a workstation by authorised staff. The computer workstations access the network via a login name and password (changed regularly). No data are stored on individual workstations. Backing up is done automatically overnight to an offsite storage area.

After the trial has been completed and the reports published, the data will be archived in a secure physical or electronic location with controlled access by permission of the chief investigator and/or the TMC.

The trial data will be made available to appropriate academic parties on request from the chief investigator, in accordance with the data sharing policies of The University of Adelaide, with input from the TMC where applicable, subject to submission of a suitable study protocol and analysis plan, on publication of all initial trial results.

### Retention of personal data

Personal data will be needed to disseminate the results of the trial to the participants. Due to the nature of pregnancy research, data will be kept for a period of up to 30 years (per local site requirements) in order to follow-up on health-related issues which may become relevant in the future. At all times the personal data are to be held securely and will not be used for any other purpose.

### Protocol amendments

Any important protocol amendments (eg, changes to eligibility criteria, outcomes, analyses) will be disseminated to relevant parties (eg, TMC, DSMC, HRECs, trial participants, trial registries, regulators) as necessary.

## Assessment and reporting of safety

Assessment and reporting of adverse events and safety outcomes will follow the reporting guidelines and definitions of the NHMRC.

### Expected events

The following are considered as expected occurrences in this population of pregnant women or a result of the routine care/treatment of a participant. As such, they will be recorded on the eCRF but not reported as AEs or SAEs:
Worsening pruritusHospitalisation for worsening ICPGestational diabetes/diabetes stabilisationPre-eclampsiaAdmission in active labourAdmission for cervical ripening or induction of labourAdmission for caesarean sectionShort term (< 24 h) admission for assessment for suspected fetal compromise, including reduced fetal movements, or accelerated fetal growth and/or polyhydramniosShort term (< 24 h) admission for monitoring for hypertension, suspected preterm labour, or pre-labour rupture of the membranes

Such admissions are not AEs, but the underlying reason may be.

However, admission for other fetal or maternal issues, including IUGR, reduced movements, severe hypertension, seizures (eclampsia), antepartum haemorrhage, pre-term labour, pre-term premature rupture of the membranes (PPROM), psychiatric disorder, social issues, unstable lie/abnormal lie, amnioreduction, and other issues are to be reported as AEs, and may well be considered SAEs, especially if the admission is for > 24 h.

The following perinatal outcomes are pre-specified outcomes and will not be reported as AEs/SAEs:
NNU admissionPreterm delivery (< 37 completed weeks gestation)Meconium staining of the amniotic fluid or placentaNeed for phototherapyNeed for respiratory support – headbox oxygen

The following perinatal complications are to be reported as AEs and may be considered as SAEs:
Neonatal seizuresEncephalopathy treated with hypothermiaNeed for respiratory support – ventilation via an endotracheal tube or nasal CPAPSepsis requiring > 5 days antibiotics with symptoms or confirmed blood or cerebro-spinal fluid (CSF) culture

The period for safety reporting is from first dose of study treatment until 6 weeks post-delivery.

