## Background

Intrahepatic cholestasis of pregnancy (ICP) is the most frequent liver disorder specific to pregnancy, with an annual Australian incidence of 0.6–0.8% [1]. Its cardinal features are maternal pruritus and increased serum bile acids (BA), commonly towards the end of the third trimester. The pruritus, though often mild, can occasionally be extremely severe, causing major skin excoriations, profound sleep disturbances and associated psychopathology, with iatrogenic premature delivery for symptom relief. ICP can also cause severe liver dysfunction and jaundice. BA are formed in the liver and secreted in the bile into the intestine, where they emulsify fat in the ingested food and enable its uptake into the liver, where the BA are recycled. In ICP, this cycle of “enterohepatic circulation” is inhibited and serum BA concentrations increase, providing a marker for the disorder [2]. Increased rates of postpartum haemorrhage (PPH) reported in early studies [3] have not been confirmed in more recent larger datasets [4]. Gallstones may be present more often in these women [5]. Women with hepatitis C infection have a higher incidence of ICP [6]. Maternal symptoms typically resolve after birth, but affected women have an increased risk of hepatobiliary disease in later life [6]. There are few data for long term outcome in the children of mothers with ICP [7].

ICP has been associated with increased fetal risks, including spontaneous preterm birth, fetal hypoxia and compromise (including meconium-stained liquor) and unexpected intrauterine fetal death [3]. Higher concentrations of circulating BAs are associated with increased fetal risks, including spontaneous preterm birth, asphyxial events and stillbirth [8, 9]. Early onset (less than 34 weeks gestation) severe (defined as serum BA > 40 μmol/L) ICP is a rare disorder with an Australian incidence of 0.1% per annum [1].

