### Rifampicin

The dose of rifampicin is 300 mg twice daily. Administration of rifampicin will be withheld if, during treatment, there is a rise of serum ALT above 200 U/L, and the management of such patients discussed with senior clinicians, including CI [name] and/or CI [name], to decide about continuation of rifampicin therapy. Rifampicin will be weaned after birth by 150 mg every 3 days.

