### Possible side-effects

Commonly, body fluids, including urine, stools, saliva, sputum, sweat and tears, turn red-orange.

Other side effects from rifampicin are not common, but can include headache, muscle pain, bone pain, heartburn, upset stomach, vomiting, stomach cramps, chills, diarrhoea, urticaria, sores on skin or in the mouth, fever, or jaundice.

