### Data analysis

A detailed Statistical Analysis Plan will be developed by the trial statistician (who is independent of the Sponsor) and agreed by the Trial Management Committee (TMC) before the analysis is undertaken. The analysis and presentation of results will follow the most up-to-date recommendations of the CONSORT group. Analyses will be completed in STATA® version 13.0 or later.

All analyses will follow the intention to treat principle, i.e. data from all randomised woman and babies will be analysed according to the treatment they were allocated to irrespective of the treatment they received or whether they received any treatment at all.

Blinding will not be possible for participants and care providers, because of the open nature of the interventions, nor will the DSMC be blinded to allocation in their assessment of outcomes and safety, but the outcome data will be blinded to the data analysts by concealing the group allocation prior to the analysis.

Demographic and clinical data will be summarised with counts and percentages for categorical variables, means (standard deviations) for normally distributed continuous variables and medians (with interquartile or simple ranges) for other continuous variables.

For the primary outcome, the effectiveness of the interventions will be assessed by calculating the differences in mean pruritus score with 95% confidence intervals (CI), determined with a linear regression model, using Generalised Estimating Equations (GEEs).

All comparative analyses will be performed adjusting for stratification variables and baseline measures of the outcome, where relevant. Binary outcomes will be analysed using log binomial regression models. Results will be presented as adjusted risk ratios plus 95% CIs. If the model is unstable, log Poisson regression models with robust variance estimation will be used [34]. Continuous outcomes will be analysed using linear regression models, and results will be presented as adjusted differences in means (with 95% CIs). Analysis of outcomes that are measured repeatedly over time (severity of pruritus and biochemical markers) will use repeated measures analysis techniques, including GEEs and/or random effects.

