### Procedures for recording AEs

Assessment for AEs are to be conducted at each study visit. All AEs occurring during the trial that are observed by the PI/delegate or reported by the participant will be recorded in the eCRF, whether or not attributed to the study drug. In recording the AE on the eCRF, whether the event was an SAE or not will be entered. All AEs determined to be an SAE must be reported following the guidelines and time frames below.

All AEs and SAEs will be followed-up to resolution with a start date and an end date recorded.

It will be left to the PI’s clinical judgement to decide whether or not an AE is of sufficient severity to require the participant’s removal from the trial. A participant may also voluntarily withdraw from treatment due to what she perceives an intolerable AE. If either of these occurs, the participant must be given appropriate care until symptoms cease or the condition becomes stable.

Unexpected serious adverse maternal and neonatal events (SAEs) will be reported to the sponsor within 24 h. The sponsor will forward these reports and their review of the SAE to the DSMC and the HREC that provided REC approval within 72 h of receipt.

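### The AE/SAE exemption for admissions with worsening ICP has no hepatic exception, so an admission with liver deterioration on rifampicin can be filed as disease and be absent from the listings the DSMC reviews

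*Protocol article*

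**What the plan says.** Under Expected events, the protocol article lists occurrences regarded as normal for this population and states that "they will be recorded on the eCRF but not reported as AEs or SAEs". Worsening itch is on the list, and so is admission for worsening ICP. The ICP item has no time limit and no exception for liver findings. Two other admission items on the same list count as exempt only when they last under 24 h.

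Two qualifications follow the list. The first is "Such admissions are not AEs, but the underlying reason may be". The second names other maternal and fetal reasons for admission and closes with "and other issues are to be reported as AEs, and may well be considered SAEs, especially if the admission is for > 24 h".

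Four other sections bear on the rule:

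- **Liver effects.** Background: "ICP can also cause severe liver dysfunction and jaundice". The rifampicin side effects, described as uncommon, end with "sores on skin or in the mouth, fever, or jaundice". The UDCA side effects name nothing hepatic.
- **ALT rule.** Rifampicin: "Administration of rifampicin will be withheld if, during treatment, there is a rise of serum ALT above 200 U/L". Such cases are then discussed with senior clinicians.
- **Blinding.** Data analysis: "Blinding will not be possible for participants and care providers".
- **Recording and review.** AEs are entered "whether or not attributed to the study drug" (Procedures for recording AEs). The DSMC receives three-monthly listings of AEs, SAEs, deviations and breaches, and it assesses safety after 50 women.

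**The concern.** The protocol foresees a hepatic harm of the test drug and sets a laboratory trigger for it. It also says that the disease can produce the same picture. The exemption depends on the label given to the admission, and the article gives no criterion that separates worsening ICP from drug injury. The label is applied by clinicians who know the allocation.

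What is at stake is safety monitoring while the trial runs. The DSMC's routine material is AE and SAE listings, and the article does not say that exempt events held only on the eCRF reach it. With 1:1 allocation, the look after 50 women has about 25 per arm, so one or two misfiled hepatic admissions could change how that committee reads the data.

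**Working it through.** The plan states no figure on this point, so there is none to reproduce. The check sets the sections side by side and applies them to three hypothetical women on rifampicin.

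| Case | Which text applies | Result |
|---|---|---|
| A. On-treatment ALT rise above 200 U/L, not admitted | Nothing on the exempt list covers it | Recordable as an AE whatever the cause |
| B. Same rise with jaundice, admitted, clinician suspects rifampicin | Admissions for other issues | AE, possibly SAE |
| C. Same findings as B, admitted, clinician judges ICP has worsened | Exempt list, then the sentence on the underlying reason | Admission exempt; the hepatic event may be an AE; seriousness not settled |

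**Step 1.** B and C have identical findings and differ only in presumed cause. The recording section makes attribution irrelevant to whether an AE is entered. The exemption makes it relevant again for this type of admission.

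**Step 2.** The sentence on the underlying reason narrows the gap in case C but leaves two things open. It is permissive and gives no criterion. It also says that the admission is not an AE, without saying whether being admitted makes the underlying hepatic event serious.

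**Step 3.** The route for other issues opens only once someone has decided that the cause is not ICP, which is the uncertain judgement.

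**Step 4: how far the size can be taken.** Let n be the women on rifampicin, p the risk of an admission with liver deterioration, and f the share of those admissions labelled as worsening ICP and not otherwise reported. The expected number absent from the listings is n × p × f. The inputs are n = 108 / 2 = 54 in the full arm and about 50 / 2 = 25 at the safety look. The documents give neither p nor f. Taking p from 2% to 15% purely as an assumption:

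| p | n × p, full arm | n × p, 50-woman look |
|---|---|---|
| 2% | 54 × 0.02 = 1.1 | 25 × 0.02 = 0.5 |
| 5% | 54 × 0.05 = 2.7 | 25 × 0.05 = 1.3 |
| 10% | 54 × 0.10 = 5.4 | 25 × 0.10 = 2.5 |
| 15% | 54 × 0.15 = 8.1 | 25 × 0.15 = 3.8 |

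These are ceilings, reached only at f = 1. At f = 0 nothing is lost. Over the assumed range, the number absent runs from 0 to about 8 in the full arm and from 0 to about 4 at the safety look.

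**Step 5: direction.** The exemption applies to both arms. Misfiled drug injury would lower the SAE count on rifampicin. If rifampicin controls the disease better, more exempt ICP admissions would fall in the UDCA arm and lower its SAE count. The documents do not allow these to be netted.

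**The case against.** A reader might infer that admitted liver injury on rifampicin is necessarily counted as disease and lost as a serious event. The text does not say so. It exempts an admission, not jaundice or an ALT rise. It leaves the underlying reason reportable, and it makes an admission recognised as drug injury reportable as an AE and possibly an SAE. The strong reading has to assume the misclassification it sets out to show.

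Other routes to detection exist:

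- Rifampicin cases above the ALT trigger are discussed with senior clinicians.
- Exempt events stay on the eCRF.
- Serial ALT, bilirubin, GGT and bile acids are secondary outcomes analysed by arm.
- The DSMC is unblinded, and its charter, which is not shown, may ask for more than listings.
- The full protocol may define worsening ICP.

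The assumed risks may also be too high. The article calls these side effects uncommon. It also cites a survey of 28 pregnancies with no reported adverse effects, for which the one-sided 95% upper limit is 1 − 0.05^(1/28) = 10%. That was a retrospective clinician questionnaire, so it is weak evidence either way.

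Much of this stands, and it limits the point to what can happen. It does not close the gap. Discussion with senior clinicians concerns treatment and is not a safety report. The liver tests are compared as outcomes, and the article plans no interim analysis. The exempt list is itself a stated rule, so the point is not a complaint about detail that the article leaves out.

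**Conclusion.** The point holds as a weakness in a stated reporting rule. An admission with liver deterioration on rifampicin can be classed as worsening ICP by an unblinded clinician and be absent from the AE and SAE listings. The qualifying sentence makes reporting discretionary and leaves seriousness unsettled.

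Two stronger readings are not supported. One is that the SAE comparison is biased in favour of rifampicin; the direction is unknown because the exemption works in both arms. The other is that the SAE listing would show no such events; that is the worst case on an assumed risk, with every admission given the ICP label. The size cannot be derived from the documents.

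The conclusion assumes that no unseen document supplies a hepatic exception or brings exempt admissions before the DSMC. The rule should be amended because hepatic deterioration is the only harm for which the protocol sets a laboratory trigger to withhold rifampicin, and the data needed are already collected.

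**What to change.** Reconcile Expected events with the ALT rule and the side-effect list for rifampicin. The change is to reporting only and leaves every dose, threshold and treatment decision as it is.

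1. State that the exemption for ICP admissions does not cover an admission with (a) new jaundice, (b) an on-treatment rise of ALT from baseline to above the protocol's existing trigger, or (c) study drug withheld because of liver tests.
2. Report these events as AEs, and as SAEs if the woman is admitted, in both arms and regardless of presumed cause.
3. List them by arm for the DSMC, together with the ICP admissions that remain exempt, so that the committee can see how the label is being used.

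The words on-treatment and from baseline in (b) are needed because the eligibility criteria set no upper ALT limit. Without them, liver disease present at entry would generate reports.

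The cost is an amendment to one section and a short listing from ALT, bilirubin and admission data already on the eCRF. There will be some extra reports, and part of them will reflect ICP and not the drug. Their number cannot be estimated from the documents.

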### Inclusion criteria

Women are considered eligible for inclusion into the trial with the following criteria:
Severe ICP (defined as pruritus with increased total serum BA ≥40 μmol/L) confirmedViable pregnancy between 14^+ 0^ and 33^+ 6^ weeks gestation inclusive (as determined by ultrasound pregnancy dating)No known lethal fetal anomalySingleton pregnancyObstetric care in a consultant-led unitAged 18 years or overWritten informed consent has been obtained

Standardisation of serum BA concentration measurements: participating units will have tested a series of serum samples sent out from Adelaide, for comparison and correlation with the Adelaide values, and subsequent adjustment of the results from the local laboratories to enable standardisation of the results across the trial. Similar quality control testing will be carried out every 12 months.

Women who present with non-severe ICP (total serum BA < 40 μmol/L) between 14^+ 0^ and 33^+ 6^ weeks gestation, and who then progress, with or without UDCA treatment, to severe ICP (total serum BA ≥40 μmol/L) prior to 34^+ 0^ weeks gestation, are eligible for entry into the trial, providing they are willing to accept random allocation to treatment (with a wash-out period of any pre-existing UDCA treatment for 4–7 days to enable baseline biochemical data to be obtained, and confirm eligibility only if serum BA were measured ≥40 μmol/L while not taking UDCA), they meet the other inclusion criteria and they do not meet any of the exclusion criteria (below), in which case they will be randomised either to rifampicin therapy or to commence/continue with UDCA therapy.

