## Interventions

The intervention under test is rifampicin (rifampicin) tablets 300 mg twice daily and the comparator treatment is ursodeoxycholic acid (UDCA) tablets up to 2000 mg daily, prescribed as per the usual local protocols.

Women meeting the inclusion criteria and consenting to participation will be randomly allocated to treatment with rifampicin or UDCA at study entry. The duration of treatment will range from 1 day to a maximum of 28 weeks, for a participant randomised at 14 weeks who does not deliver until 42 weeks.

Within the trial, both UDCA and rifampicin are usually dispensed by the local hospital pharmacy.

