**Table 1 Tab1:**
[figure not shown]
Trial Timeline

*GA* gestational age, *ALT* alanine transaminase, *LFTs* liver chemistry analysis, *INR/APTT* International Normalised Ratio/Activated Partial Thromboplastin Time

Notes to Table 1

^1^All screening assessments are part of normal clinical practice

^2^Bile acid samples need to be drawn shortly before a scheduled dose of UDCA, though fasting is not required. Women previously prescribed UDCA for treatment of mild ICP, and agreeing to randomisation, will have basal assessments performed 4–7 days after ceasing such therapy prior to randomisation into the trial

^3^Study treatment started after randomisation. Dose to be adjusted by PI if indicated by symptoms and/or blood tests taken during normal clinical practice

^4^Adverse events will be recorded from study entry until post-delivery discharge of woman and baby. All SAEs are to be reported to the Coordinating Centre within 24 h of Investigator knowledge

Women eligible for the trial, whether or not they participate, will be asked about their willingness to take part in a subsequent trial of planned delivery of such affected women at 36^+ 0^ weeks gestation compared with expectant management in terms of neonatal outcomes.

Women taking part in the study will be asked about any other drugs that have been prescribed or initiated after randomisation. If such medications include agents known to have a significant interaction with rifampicin, then a woman taking rifampicin will be asked to withdraw from the study, although any data obtained until withdrawal will be included, and any pregnancy outcome data will be recorded (with her consent).

Participating women will also be asked at recruitment about any antibiotics they may have taken in the 3 months prior to recruitment, as well as any progesterone supplements they may have taken.

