### Baseline assessments

Baseline data, including all demography, itch chart results, serum BA concentrations, other serum analytes, viral serology and coagulation profiles, including prothrombin time and activated partial thromboplastin time (recorded within 7 days prior to randomisation, and 4–7 days after cessation of any previously initiated UDCA therapy), are entered on the web-based data base. The itch chart is a previously validated 100 mm visual analogue score where the participant is asked to score her worst itch in the previous 24 h [27]. All laboratory data are measured in the routine hospital laboratories for each centre.

Other biological samples, including serum, urine, faeces, liquor and placenta, may also be collected (with participant consent) under separate protocols and stored for later assessment.

On completion of these details, the database issues a randomisation notification to the site PI/delegate. A prescription for the allocated study treatment is written by the local PI or their delegate, using a standard clinical prescribing script, and the participant collects the study treatment from the pharmacy.

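### For women already on UDCA, the protocol's 4–7 day wash-out before randomisation falls before both stated adverse-event windows, so serious events in it need not be reported

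*Protocol article*

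**What the plan says.** All references are to the protocol article.

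- **Wash-out.** Under Inclusion criteria, women who progress to severe disease while on UDCA may be randomised "with a wash-out period of any pre-existing UDCA treatment for 4–7 days to enable baseline biochemical data to be obtained". The same sentence says sites are to "confirm eligibility only if serum BA were measured" at 40 μmol/L or more off UDCA. Note 2 to Table 1 says such women "will have basal assessments performed 4–7 days after ceasing such therapy prior to randomisation into the trial". Baseline assessments gives the timing of baseline data as "recorded within 7 days prior to randomisation, and 4–7 days after cessation of any previously initiated UDCA therapy".
- **Recording window.** Note 4 to Table 1: "Adverse events will be recorded from study entry until post-delivery discharge of woman and baby".
- **Reporting window.** Expected events, within the safety section: "The period for safety reporting is from first dose of study treatment until 6 weeks post-delivery".
- **Study entry.** Interventions says consenting women "will be randomly allocated to treatment with rifampicin or UDCA at study entry". Note 3 to Table 1 puts the start of study treatment after randomisation.
- **Routes.** Under Procedures for recording AEs, unexpected SAEs go to the sponsor within 24 hours and on to the DSMC and ethics committee within 72 hours. The DSMC section has the Chair review SAE reports as they arrive, and the committee review AE and SAE listings every three months.

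**The concern.** The wash-out is a trial procedure. Its stated purposes are baseline data and confirmation of eligibility, whereas Current practice says women who progress to severe disease are usually offered increasing UDCA doses, with rifampicin added if needed. An interruption that exists because of the trial should fall within the trial's safety surveillance, and on the stated windows it does not.

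The population is one that the Background treats as high risk: it links higher bile acid concentrations to spontaneous preterm birth, asphyxial events and stillbirth. If a fetal death occurred while a woman was off UDCA in order to qualify, nothing in the article would require it to be reported as an SAE or listed for the DSMC. The gap is widest for a woman who stops UDCA and is then not randomised, for instance because her off-treatment bile acids are below the threshold. For her, neither window ever opens.

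**Working it through.** No sample-size or power figure is involved. The check places the wash-out and the two windows on one timeline, with randomisation as day 0.

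1. **Wash-out.** It lasts 4–7 days and ends before randomisation (Inclusion criteria; Table 1, note 2). If randomisation follows the baseline sample at once, it runs from between day −7 and day −4 up to day 0.
2. **What study entry means.** Interventions places allocation at study entry. Two other sections agree: Secondary outcomes schedules the first itch assessment one week after trial entry, and Subsequent visits schedules the same visit one week after randomisation. Study entry is therefore day 0.
3. **Comparison.**

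| Interval | Opens | Closes | Overlap with wash-out |
|---|---|---|---|
| Wash-out | day −7 to −4 | before day 0 | – |
| AE recording (Table 1, note 4) | day 0 | discharge after delivery | 0 days |
| Safety reporting (Expected events) | first dose, after day 0 | 6 weeks after delivery | 0 days |

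4. **Conflict between the windows.** They differ at the start (study entry or first dose) and at the end (discharge or 6 weeks). They need reconciling whatever is decided about the wash-out.
5. **Women not randomised.** Eligibility depends on the off-UDCA bile acid value, so some women may stop UDCA and then fail to qualify. The Randomisation section issues the participant number only on randomisation, and no safety record is described for women who do not reach it.
6. **Events that depend on the window.** Expected events exempts several occurrences from AE and SAE reporting at any time. These include worsening pruritus, hospitalisation for worsening ICP, admission for caesarean section, short admissions for suspected fetal compromise, and preterm delivery. An earlier start would not make these reportable in themselves. Fetal death is not on the exempt lists. Admissions for reasons such as antepartum haemorrhage, severe hypertension or preterm labour are expressly reportable as AEs and possibly SAEs, apart from the stays under 24 hours that the exempt list covers. These are the events lost if they occur before the window opens.

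**The case against.** Several points on the other side are sound.

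- **General wording elsewhere.** Procedures for recording AEs covers all adverse events during the trial without giving a start, and the DSMC may consider harm from the conduct of the trial. The national reporting guidelines and the DSMC Charter, to which the article defers, are not shown, nor is the Table 1 grid. A reader might infer from the two windows that wash-out harms are never counted or seen. The document does not support that: an investigator could report such an event, and randomised women have itch and bile acids measured at the end of the wash-out. What stands is that no text requires reporting, and undated wording does not displace two explicit start points.
- **Study entry as consent.** On that reading note 4 could cover the wash-out. The text ties study entry to allocation, however, and the reporting window in Expected events would still open only at first dose.
- **Evidence of harm.** The Background reports that the placebo-controlled UDCA trial found no benefit on a composite of adverse perinatal outcomes. It also gives a pooled stillbirth risk ratio of 0.33 (95% CI 0.08 to 1.37) at very low certainty. Fetal harm from a few days off UDCA is not established. This lowers the stakes but does not remove the case for recording events.
- **Condensed article.** Screening logs and the handling of women not randomised may be set out in the full protocol. That is fair for the detail, but here the article states the windows itself, and they exclude the wash-out.
- **Note 1 to Table 1.** A reader might take "All screening assessments are part of normal clinical practice" as a false description of the wash-out. It refers to assessments, and note 2 discloses the UDCA cessation separately, so it is not clearly wrong.

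**Conclusion.** The point holds for women already taking UDCA at screening. Followed as written, the protocol leaves a trial-imposed interval of 4–7 days with no overlap with either AE window. Non-exempt serious events in that interval, chiefly fetal death and other reportable maternal or fetal SAEs, are not required to reach the 24-hour route or the DSMC listings. This rests on reading study entry as allocation, which three sections support; the reporting window excludes the wash-out on either reading.

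Stronger readings should be resisted. It would be wrong to say that all women with severe disease must stop UDCA, since those who present untreated are unaffected. The total exposure cannot be sized, because the document does not say how many women enter on UDCA. Nor are the women unobserved: eligibility requires obstetric care in a consultant-led unit. Adding the 7-day baseline allowance to the longest wash-out gives 7 + 7 = 14 days, but that is an outer limit from combining two maxima, not the stated wash-out.

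The between-arm comparison is not affected, because the interval precedes randomisation. No view is taken on whether, or for how long, UDCA should be stopped.

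**What to change.** 1. Reconcile note 4 to Table 1 with the reporting period in Expected events, so that one start and one end apply to AE recording and SAE reporting.
2. For women who stop UDCA for the trial, start AE and SAE recording and the 24-hour SAE route at consent, and state that consent comes before the wash-out begins.
3. Include women who start the wash-out but are not randomised, using an identifier that does not depend on randomisation.
4. Give the DSMC these pre-randomisation events as a separate listing. Keep the start of the between-arm safety comparison at randomisation.

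The cost is small: wording changes in two places, provision for data capture before randomisation, a short extra listing, and a few more days of AE recording in a subset of women. No treatment or eligibility rule changes.
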